### Statistical analysis

The statistical analysis will be based on the intention-to-treat (ITT) population. Missing data imputation will be used in order to evaluate the robustness of the primary endpoint analyses. The primary imputation method will be LOCF (last observation carried forward). The statistical analysis will be conducted for both three (EA 1: EA 2: control) and two (EA: control) groups. The null hypothesis is that there is no difference in the changes of variables between the two or three groups before and after treatment. The three groups will be compared by one-way analysis of variance (ANOVA) or the Kruskal-Wallis test for continuous variables, and chi-squared or Fisher’s exact test for categorical variables. Analysis of covariance will be performed with covariates that may affect VAS level. Post hoc analysis will be done if there is a significant difference between the three groups using the Bonferroni correction. The two (EA: control) groups will be compared by means of Student’s *t* test or Wilcoxon’s rank sum test for continuous variables, and chi-squared or Fisher’s exact test for categorical variables. A two-sided *P* value of less than 0.05 will be considered to indicate statistical significance.

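### The day-5 primary endpoint gets two unranked 5% tests, three-arm and pooled EA versus control, so a claim resting on either carries about 7.4–7.5% type I error with equal SDs

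*Protocol article*

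**What the plan says.** The Outcomes section names one primary endpoint, the change in VAS pain from pretreatment to day 5. The Statistical analysis section then plans two analyses: "The statistical analysis will be conducted for both three (EA 1: EA 2: control) and two (EA: control) groups". The null hypothesis covers both without ordering them: "The null hypothesis is that there is no difference in the changes of variables between the two or three groups before and after treatment".

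For the three-arm analysis, "The three groups will be compared by one-way analysis of variance (ANOVA) or the Kruskal-Wallis test for continuous variables". The pooled analysis uses Student's t or Wilcoxon's rank sum test. The only multiplicity provision is "Post hoc analysis will be done if there is a significant difference between the three groups using the Bonferroni correction", which sits inside the three-arm branch. The significance rule is common to all tests: "A two-sided *P* value of less than 0.05 will be considered to indicate statistical significance".

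No other section says which analysis decides. Study design and the Discussion state the aim as EA against conventional treatment, but they also describe a three-arm superiority trial and an interest in comparing the two EA regimens. The sample size section refers to one test group against one control group without saying which.

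**The concern.** One endpoint and one broad claim, that EA relieves pain, meet two tests that each use the full 5%. The Bonferroni step does not cover the choice between them. If either result can carry the claim, the trial does not hold its stated 5% level. There is also no rule for a split result, and a split is likely if local and local-plus-distal EA differ in effect, which the Discussion wants to examine. Treatment is unblinded and the endpoint is patient-reported, so the decision rule should not be left to be settled once the results are known.

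**Working it through.** **Inputs.** Two-sided 0.05 and the two tests (Statistical analysis); 1:1:1 allocation, hence 2:1 after pooling (Randomization); SDs 19 (test) and 25 (control), difference 20, 90% power, 25 evaluable and 33 randomised per arm (Planned number of subjects).

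**The plan's own figure.** n = (19² + 25²) × ((1.960 + 1.282)/20)² = 986 × 0.02627 = 25.9, so 26 per arm against the stated 25 (normal-approximation power at 25 is 89.0%). 26/0.8 = 32.5, giving 33. The size is reproduced to within one patient, for a single comparison at the full 5%.

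**Type I error, equal SDs, large samples.** Under no difference, the three-arm statistic behaves as Z₁² + Z₂² and the pooled contrast as Z₁², with Z₁ and Z₂ independent standard normals. Then

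P(either significant) = 1 − P(Z₁² < 3.841 and Z₁² + Z₂² < 5.991) = 7.5%.

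Two independent tests would give 1 − 0.95² = 9.75%. The lower figure reflects the correlation between the tests.

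**Simulation, no mean difference** (200,000 trials per row, Monte Carlo standard error about 0.06 points):

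| Per arm | SDs | F alone | Pooled Student t alone | Either |
|---|---|---|---|---|
| 25 | equal | 4.8% | 4.9% | 7.4% |
| 33 | equal | 5.0% | 4.9% | 7.5% |
| 25 | 19/19/25 | 5.2% | 7.3% | 8.7% |
| 33 | 19/19/25 | 5.1% | 7.3% | 8.7% |

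Across repeated runs, the 19/19/25 case gives about 8.6–8.8% for either test and 7.2–7.4% for Student's t alone. With Welch's t as the pooled test, either-significant is about 6.7–6.9%.

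**Why Student's t is off by itself.** At 25 per arm the true variance of the pooled difference is 19²/50 + 25²/25 = 7.22 + 25.00 = 32.22. Student's formula estimates on average [(49 × 361 + 24 × 625)/73] × (1/50 + 1/25) = 447.8 × 0.06 = 26.87. The standard error is therefore too small by a factor √(32.22/26.87) = 1.095. The critical value 1.993 acts like 1.993/1.095 = 1.82, a two-sided level of about 7%. This is a variance problem, not a multiplicity problem.

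**Sensitivity to the decision rule.** If a three-arm win counts only when some Bonferroni pair is also significant, the overall rate is 6.7–6.9% (equal SDs) or about 8.4% (19/19/25). If that pair must be EA against control, it is 5.6–5.7% or about 7.6%.

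**Power** (SDs 19/19/25, 25–26 per arm). If one EA arm has the 20-point effect and the other none, the pooled difference falls to (20 + 0)/2 = 10. F-test power is then 94–95%, pooled Student 43–44% and pooled Welch 38–40%. If both arms have the 20-point effect, all three exceed 90%.

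**The case against.** The strongest reply is that the document never says a win in either branch settles the trial, so the 7.4–7.5% rests on a decision rule the reader supplies. That stands as a condition on the figure. Under the strictest rule checked, with an EA-versus-control pair required, the equal-SD rate is only 5.6–5.7%. But the text neither states that rule nor excludes the looser one, and every rule checked exceeds 5%.

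A second reply is that the aim, EA against conventional treatment, already suggests the pooled contrast leads, and that an analysis plan not shown may rank the two. The aim is a hint, not a hierarchy. The point also does not depend on silence: the article itself commits to both tests under a joint null and one threshold.

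A reader might infer more than the documents support:

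- That testing twice costs the whole rise from 5% to about 8.7%. It does not. With SDs 19/19/25, Student's t alone is at 7.2–7.4%, and the second test adds about 1.5 points.
- That the open choice between parametric and rank tests is a further defect. An analysis plan commonly settles that, so it is no finding here.
- That the three-arm test must lead because pooling loses power. That holds only if one EA arm has no effect, which no section anticipates. The omnibus test can also reject solely because the two EA arms differ, so it does not by itself show that EA works.

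**Conclusion.** The point holds: two unranked full-level tests bear on one primary endpoint, and the Bonferroni step does not link them. If either result is taken to show efficacy, type I error is about 7.4–7.5% with equal SDs, an excess of about 2.5 points. With the plan's SDs it is about 8.6–8.8% using Student's t, mostly a variance effect, or about 6.7–6.9% using Welch's t. These figures assume normal data, 25–33 analysed per arm and no mean difference between arms. The risk of a split result is material only if the two EA regimens differ in effect. This should be fixed, but it does not undermine the design: the inflation is moderate, the tests are strongly correlated, and wording cures it.

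**What to change.** Before analysis, name one primary comparison for the day-5 VAS change at two-sided 5%. Either choice works:

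- **Pooled EA versus control first**, which matches the stated aim, with the three-arm and pairwise comparisons tested only afterwards in a fixed order.
- **The three-arm test first**, then Bonferroni-adjusted pairs, with efficacy claimed only from EA-versus-control pairs.

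Report the analysis not chosen as supportive, with an estimate and 95% CI. Specify Welch's test for the pooled contrast, since the plan itself assumes unequal SDs and pooling makes the groups 2:1.

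The cost is a few sentences in the protocol or analysis plan, no added patients, and the loss of confirmatory status for one analysis. Under the plan's SDs, Welch's test gives up some nominal power (38–40% instead of 43–44% if only one arm works), but Student's figure is bought with a type I error above 7%.

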### Outcomes

The primary endpoint is the change in Visual Analog Scale (VAS, 0–100) for pain on day 5 compared to pretreatment. Secondary endpoints include daily VAS (days 1–4), requirement of analgesics, changes of inflammatory marker (C-reactive protein), time to pain disappearance and hospital days. Daily VAS is the average of VAS measured three times a day. The requirement of analgesics includes both the amount and frequency of analgesics administered daily.

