### Planned number of subjects and period

A total of 99 patients will be enrolled for 2 years. Sample size calculation was performed for achieving a 90% power at the 5% level of significance.. The sample size was calculated as in Fig. 2. The population standard deviation (*σ*) was determined as the largest value according to a previous study [18]. Therefore, the standard deviations are 19 for the test group and 25 for the control group. The expected minimum clinical difference of 20 has been defined; this is the difference between the test group and the control group. This is achieved by enrolling 25 evaluable patients in each treatment group. To allow for a possible 20% dropout rate, 33 patients will be randomised to each group. The enrolled patients will be followed up for 1 month to monitor any delayed adverse events (see Fig. 3 for the schedule of enrollment, interventions, and assessments..

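### The named tests for VAS change are unadjusted, and the planned ANCOVA is neither ranked nor tied to pretreatment VAS; making it primary with that covariate would gain precision at no cost

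*Protocol article*

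**What the plan says.** The Outcomes section of the protocol article sets the endpoint: "The primary endpoint is the change in Visual Analog Scale (VAS, 0–100) for pain on day 5 compared to pretreatment".

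The Statistical analysis section frames the hypothesis in the same terms: "The null hypothesis is that there is no difference in the changes of variables between the two or three groups before and after treatment". It then lists the tests.

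- Three groups: "The three groups will be compared by one-way analysis of variance (ANOVA) or the Kruskal-Wallis test for continuous variables".
- Next sentence: "Analysis of covariance will be performed with covariates that may affect VAS level". No covariate is named, and the text does not say whether this analysis is primary or supportive.
- Pairwise follow-up: Bonferroni-corrected, if the three-group result is significant.
- Pooled EA against control: the "groups will be compared by means of Student’s" t test or Wilcoxon's rank sum test. No adjusted version is mentioned for this comparison.

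The section on planned number of subjects gives 90% power at the 5% level, a difference of 20, 25 evaluable and 33 randomised per group. On variability it says that "the standard deviations are 19 for the test group and 25 for the control group". It does not say whether these are SDs of the change or of VAS at one time point.

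**The concern.** A change from baseline usually depends on the baseline: a patient who starts with more pain has further to fall. Subtracting the baseline in full removes its influence exactly only when the slope of day-5 VAS on pretreatment VAS is 1. With a shallower slope, subtraction over-corrects. That adds variance and leaves part of any chance difference in starting pain in the treatment contrast. Regressing on pretreatment VAS estimates the slope instead of fixing it.

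The inclusion criteria set no minimum pain score, so starting VAS may vary widely, and the arms are small. The stake is precision, together with how far the result can be moved by an imbalance that happens to occur. A second cost is that the same endpoint has an unadjusted and an adjusted analysis with no stated order, in a trial whose treatment is not blinded.

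**Working it through.** **Inputs.** From the article: SDs 19 and 25, difference 20, two-sided alpha 0.05, power 90%, dropout 20%, 25 evaluable and 33 randomised per group. Assumed, because the article does not give them: correlation ρ between pretreatment and day-5 VAS of 0.3 to 0.7; equal variances at the two times; baseline SD of 20 to 25.

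**1. The plan's own figure.** An unadjusted comparison of two means gives n = (19² + 25²) × (1.960 + 1.282)² / 20² = 986 × 10.51 / 400 = 25.9, so 26 per group against the stated 25. Then 26 / 0.8 = 32.5, so 33 randomised, as stated. The sample size therefore matches an unadjusted two-group comparison. Both 26 (evaluable) and 33 (all randomised) are used below.

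**2. Variance ratio.** With a common variance s²:

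- change score: 2s²(1 − ρ)
- ANCOVA: s²(1 − ρ²)
- ratio: (1 + ρ)/2

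This is 0.65, 0.75 and 0.85 at ρ = 0.3, 0.5 and 0.7. Standard errors are 19%, 13% and 8% smaller (square roots 0.81, 0.87, 0.92). Put the other way, the change score needs 1/0.85 to 1/0.65 times as many patients, that is 18% to 54% more.

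The direction does not depend on equal variances. With SDs b at baseline and d at day 5, the change-score variance minus the ANCOVA variance is (b² + d² − 2ρbd) − d²(1 − ρ²) = (b − ρd)², which is never negative.

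**3. Power if 19 and 25 are SDs of the change.** The root mean square SD is √(986/2) = 22.2, and the adjusted SD is 22.2 × √((1 + ρ)/2) = 17.9, 19.2 and 20.5. Bonferroni for three pairs is taken as 0.05/3 = 0.0167. Power from the noncentral t distribution, rounded:

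| Per arm | Alpha | Unadjusted | ρ = 0.3 | ρ = 0.5 | ρ = 0.7 |
|---|---|---|---|---|---|
| 26 | 0.05 | 89% | 98% | 96% | 93% |
| 26 | 0.0167 | 78% | 93% | 89% | 85% |
| 33 | 0.05 | 95% | 99% | 99% | 97% |
| 33 | 0.0167 | 88% | 98% | 96% | 93% |

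Pooled or unequal-variance degrees of freedom move these by about 0.2 points at most.

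**4. Power if 19 and 25 are SDs of VAS at one time point.** The change-score SD is 22.2 × √(2(1 − ρ)) and the ANCOVA SD is 22.2 × √(1 − ρ²). At 26 per arm and alpha 0.05, power is 77%, 89% and 98% for the change score against 92%, 96% and 99% for ANCOVA at ρ = 0.3, 0.5 and 0.7.

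**5. Chance imbalance.** The difference in mean baseline VAS between two arms of 26 has SD 20 × √(2/26) = 5.5 or 25 × √(2/26) = 6.9. The change contrast, taken given the baselines, moves by (1 − ρ) of the imbalance. For a one-SD imbalance that is 3.9 to 4.9 points at ρ = 0.3, 2.8 to 3.5 at ρ = 0.5 and 1.7 to 2.1 at ρ = 0.7, against a target of 20.

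**The case against.** The strongest reply is that adjustment is already planned. The ANOVA sentence is a general rule for continuous variables and would also serve C-reactive protein and hospital days. The ANCOVA sentence is the only test sentence that mentions VAS, and pretreatment VAS is the most obvious covariate it could mean. A covariate list is commonly left to the analysis plan, which is not shown.

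Much of this stands. A reader might infer that the trial does not adjust at all, or that the ANCOVA is a mere extra. The article supports neither, because it gives the ANCOVA no rank in either direction. An unnamed covariate list alone would not be a finding. What remains is in the published text: the hypothesis about changes is followed by unadjusted tests, the pooled comparison has only unadjusted tests, and nothing says which result decides.

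A reader might also infer that the unadjusted result is biased, or that baseline imbalance passes into it in full. Neither holds. Under randomisation the change contrast is unbiased on average and its test is valid, and regression to the mean does not favour one arm on average. Only the fraction (1 − ρ) of an imbalance reaches the estimate. Nor should it be said that randomisation ignores pain: the article describes blocks and is silent on strata.

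Finally, the power gain is uncertain. It depends on ρ, on what the planning SDs describe, and on how many patients are analysed. The analysis is intention-to-treat with last observation carried forward, and patients discharged early are contacted at day 5, so the number analysed may be nearer 33 than 26.

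**Conclusion.** The point holds as a matter of efficiency and clarity, not validity. The article attaches unadjusted tests to the VAS change and leaves the ANCOVA unranked, with pretreatment VAS unnamed.

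That adjustment does not lose precision, apart from one degree of freedom, follows from the algebra. Its size rests on assumptions: ρ of 0.3 to 0.7, equal variances and, for the main table, SDs of 19 and 25 read as SDs of change. The largest gain is in the Bonferroni contrasts at 26 per arm, at 7 to 16 points, against a loss of about 11 points from the correction itself (89% to 78%). It would be tempting to say that adjustment pays for the multiplicity correction. That is so around ρ = 0.5 or below, but not at 0.7. The smallest gain in that table is at 33 per arm and alpha 0.05, about 2 to 4 points. If the SDs describe a single time point and ρ is 0.7, it is about 1 point at 26 per arm. The change is worth making, but the trial does not fail without it.

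**What to change.** State in the Statistical analysis section that the primary analysis is an ANCOVA of day-5 VAS (or, equivalently for the treatment effect, of the change) on treatment arm, with pretreatment VAS as a pre-named covariate. Use this model for the three-group test, the Bonferroni pairwise contrasts and the pooled EA versus control contrast. List the unadjusted ANOVA/Kruskal-Wallis and t/Wilcoxon tests as sensitivity analyses. Any further covariates should be named at the same time or left out of the primary model.

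The cost is a sentence or two of text. Pretreatment VAS is already needed to form the endpoint, so no data, visits or patients are added. The article reports the trial as still recruiting with no interim analysis planned, so on that status the change can be made before outcomes are compared by arm.

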### Interventions and electroacupuncture procedures

Local EA is given in group EA 1, while local with distal EA is given in group EA 2, additionally. The EA 1 group receives the same SOC therapy in combination with EA therapy at a total of two acupoints including *Zhong Wan* (CV12) and *Shang Wan* (CV13). The EA 2 group also receives the same SOC therapy in combination with EA therapy at a total of 14 acupoints including *Zhong Wan* (CV12), *Shang Wan* (CV13), *He Gu* (LI4), *Nei Guan* (PC6), *San Yin Jiao* (SP6), *Xuan Zhong* (GB39), *Zu San Li* (ST36), and *Shang Ju Xu* (ST37) (Fig. 1) [14, 16, 17]. Electric stimulation is applied with mixed frequencies (30 and 3 Hz). Each EA session lasts 15 min (STN-330 electronic stimulator, Stra Tek Co., Ltd., Gyeonggi-do, Korea). Both EA groups receive auricular acupuncture therapy at a total of five auricular acupoints, including Sympathetic, *Shen Men*, Abdomen, Pancreas gall, and Spleen, alternately at the right or left side, whenever EA is given. Both EA groups undergo one session of EA daily from day 1 until day 4, or until pain resolves.

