### Data management

Double checks for data values will be performed by a trained research assistant after completion of final data collection. A data and safety monitoring committee is not required since the acupuncture study has minimal risks. Periodic data monitoring and audit for the important aspects of the trial will be conducted by two independent, trained investigators. The final data will be assessed by the first author and independent statistician. An interim analysis is not planned. The information of patients discharged before day 5 will be collected from telephone or outpatient clinic at day 5, which will be included in the analysis. For those who died during the study, only the data before death are included in the analysis.

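### Time to pain disappearance is a time-to-event endpoint, but the plan offers only complete-data tests and gives no value to patients whose pain has not resolved or who die first

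*Protocol article*

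**What the plan says.** Only the protocol article is at hand. Its relevant statements are these.

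- **Endpoint.** The Outcomes section ends its list of secondary endpoints with "changes of inflammatory marker (C-reactive protein), time to pain disappearance and hospital days".
- **Tests.** The Statistical analysis section compares three groups by one-way ANOVA or "the Kruskal-Wallis test for continuous variables, and chi-squared or Fisher’s exact test for categorical variables". It compares two groups (EA and control) by Student's *t* "test or Wilcoxon’s rank sum test for continuous variables". Analysis of covariance is added for VAS. No time-to-event method is named.
- **Missing data.** The same section states an intention-to-treat population and says "Missing data imputation will be used in order to evaluate the robustness of the primary endpoint analyses". Last observation carried forward is the main method. That rule is tied to the primary endpoint.
- **Deaths.** Data management says "For those who died during the study, only the data before death are included in the analysis".
- **Early discharge.** Data management also has a sentence that begins "The information of patients discharged before day 5 will be collected from telephone or outpatient clinic at day 5, which will be included in the" and so keeps these patients among those analysed.
- **Treatment window.** The interventions section says "Both EA groups undergo one session of EA daily from day 1 until day 4, or until pain resolves".
- **Follow-up.** The section on planned number of subjects gives one month of follow-up, with adverse events as its stated purpose.

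**The concern.** A time to resolution exists only for patients whose pain resolves while someone is recording it. ANOVA, *t* and rank tests need a value, or at least a rank, for every patient. The method list has a class for continuous and a class for categorical variables and none for event times. An analyst who follows it will therefore treat this endpoint as continuous and must decide privately what to enter for a patient still in pain, or for one who died.

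That choice matters. If unresolved patients are left blank, standard software drops them; they are the slowest cases and, if EA works, they are mostly controls. If they are given the last day observed, the difference in means is truncated. If patients are censored early at different rates in the arms and the censoring day is entered as the resolution day, a difference can appear where none exists. Treatment is open after randomisation, so a handling rule settled after the data are seen would also be open to question.

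**Working it through.** **1. The plan's own figures.** The article gives no figure for this endpoint. Its sample size concerns VAS: (1.960 + 1.282)² × (19² + 25²) / 20² = 10.507 × 986 / 400 = 25.9, so 26 per group against the stated 25, and 26 / 0.8 = 32.5, so 33 randomised as stated. This agrees closely and is used below only for group sizes: 33 controls and 2 × 33 = 66 EA patients.

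**2. Is unresolved pain to be expected?** Two places in the article say so. EA may run through day 4 unless pain has resolved earlier, so pain lasting that long is foreseen. The sample size also assumes a 20-point difference in VAS change at day 5. With baselines equal on average by randomisation and an EA mean that cannot be below 0, the expected control mean at day 5 is at least 20. On a 0–100 scale, if a fraction *p* has VAS above 0, the mean is at most 100*p*, so *p* ≥ 20/100 = 20%. If disappearance meant VAS of 10 or less (an assumption), 100*p* + 10(1 − *p*) ≥ 20 gives *p* ≥ 10/90 = 11%. Both are lower bounds that hold if the trial's own hypothesis is true.

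**3. Size of the shift in means (illustration).** Assumptions: exponential times rounded up to whole days, a common cut-off at day 5, 30% of controls unresolved then, hazard ratio 1.5 for resolution. Let *q* be the daily probability of remaining in pain.

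- Control: *q* = 0.30^(1/5) = 0.786. EA: *q* = 0.30^(1.5/5) = 0.697, with 0.30^1.5 = 16% unresolved.
- Full mean, 1/(1 − *q*): 4.67 and 3.30 days, difference 1.37.
- Capped at day 5, (1 − *q*⁵)/(1 − *q*): 3.27 and 2.76 days, difference 0.51.
- Unresolved dropped, (capped mean − 5*q*⁵)/(1 − *q*⁵): 2.53 and 2.32 days, difference 0.21.

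The simulation below gave 1.38, 0.52 and 0.22.

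**4. Power.** Simulation of 66 EA against 33 control, 1,500 trials per setting, two-sided 5%. The range of unresolved controls is assumed.

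| Controls unresolved at day 5 | Hazard ratio | Log-rank | Rank test, unresolved last | *t*, capped at day 5 | Rank test, unresolved dropped | Mean difference in days: full / capped / dropped |
|---|---|---|---|---|---|---|
| 10% | 1.5 | 0.437 | 0.377 | 0.432 | 0.222 | 0.70 / 0.50 / 0.32 |
| 10% | 2 | 0.869 | 0.800 | 0.865 | 0.585 | 1.06 / 0.80 / 0.55 |
| 30% | 1.5 | 0.373 | 0.343 | 0.320 | 0.091 | 1.38 / 0.52 / 0.22 |
| 30% | 2 | 0.814 | 0.765 | 0.771 | 0.241 | 2.03 / 0.88 / 0.40 |
| 50% | 1.5 | 0.288 | 0.282 | 0.245 | 0.069 | 2.37 / 0.42 / 0.13 |
| 50% | 2 | 0.716 | 0.687 | 0.620 | 0.107 | 3.65 / 0.77 / 0.26 |

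At hazard ratio 1 every method rejects in about 4% to 6% of trials. Dropping patients costs most of the power; ranking them last or capping costs little.

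**5. Unequal early censoring counted as resolution.** Assume 30% unresolved at day 5 and no true difference. Let 30% of one arm and 5% of the other be assigned a censoring day among days 1 to 3, entered as the event if pain was still present. The rank test then rejects in about 19% of trials (3,000 simulated), with a spurious gap of 0.39 days in favour of the arm censored more. At hazard ratio 1.5 the rejection rate moves from 0.32 up to 0.61, or down to 0.06, depending on which arm that is.

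**The case against.** The strongest reply is that this is a condensed article. It never assigns time to pain disappearance to a particular test, and a fuller protocol or analysis plan may name a survival method. That stands in part and keeps the point minor. The article is not silent, however: it gives a method list by variable type, and within that list the endpoint has no suitable place.

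Four stronger readings are tempting, and the documents do not support them.

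- *Patients discharged early are censored.* They are not: contact by telephone or clinic at day 5 is planned, and the information enters the analysis. At most, one contact may date the resolution only to an interval.
- *Pain observation ends at day 5.* This is inferred from the VAS endpoints. No sentence sets the window for this endpoint, and the schedule figure is not shown. If pain were followed until it resolved, censoring at a fixed day would disappear and the deaths would remain.
- *The listed tests bias the comparison toward no difference.* This is true of dropping unresolved patients, and of capped means read as full means. It is not general. A rank test with unresolved patients ranked last keeps its error rate and nearly matches the log-rank test, and unequal early censoring can create a difference.
- *The plan drops unresolved patients.* Nothing says so, and the intention-to-treat statement points the other way. It does not say what value those patients receive.

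A capped mean is also a legitimate quantity if declared as such: with complete follow-up to day 5 it is the restricted mean. It misleads only when reported as the mean time to resolution.

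**Conclusion.** The point holds in a limited form. The listed tests presuppose a value for every patient, and the article supplies none for those whose pain is unresolved when observation ends or who die first. Such patients are foreseeable: if the trial's own 20-point assumption is true, at least 20% of controls would have VAS above 0 on day 5.

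The direction and size of any error depend on handling that is not stated. Under the assumed exponential times and day-5 cut-off, a true difference of about 1.4 days (30% unresolved, hazard ratio 1.5) is reported as 0.5 if capped or 0.2 if unresolved patients are dropped. Unequal early censoring raises false rejection to about 19% under the assumed 30% and 5% rates. These figures are illustrations, because the article gives no resolution rates. The primary VAS analysis and the sample size are unaffected, so this is a minor point.

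**What to change.** Add two or three sentences to the Statistical analysis section, before any comparison by arm is made:

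- Define the window over which pain is observed for this endpoint and the VAS level that counts as disappearance.
- Analyse it with Kaplan-Meier curves and a log-rank test, reporting a hazard ratio or the restricted mean time to a stated day. Censor patients with unresolved pain at their last pain assessment.
- Alternatively, keep the Kruskal-Wallis and Wilcoxon tests and rank unresolved patients last. This suits a common end of observation; patients lost before it are better handled by the log-rank test.
- Never count death as resolution. For example, carry a patient who dies with unresolved pain as unresolved to the end of the window.
- For patients discharged early, use the planned day-5 contact, ask on which day the pain went, and do not censor at discharge.

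The cost is the wording and one added question at a contact already planned. Standard software suffices, and no extra patients, visits or measurements are needed.

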### Randomization

Patients will be randomized in a 1:1:1 fashion to receive EA1, EA2, and the control group. Block randomization is performed using Random Allocation Software version 1.0.0. A person who is not involved this study creates random numbers before the first subject enrolls after IRB approval. Then, the random numbers are kept in sealed envelopes in the order of their creation. An independent hospital staff member will prepare the sealed envelopes to ensure concealment of the allocation sequence. The numbers are handed over to assistants (independent researchers). After randomization, the treatment method is not blinded.

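### If the plan's own SDs (19 and 25) hold with equal mean changes, Student's t test on the pooled 2:1 EA-versus-control comparison has a size of about 7.3%, not 5%

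*Protocol article*

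**What the plan says.** All references are to the protocol article.

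- **Statistical analysis** plans two sets of comparisons: "The statistical analysis will be conducted for both three (EA 1: EA 2: control) and two (EA: control) groups". For the second set it states "The two (EA: control) groups will be compared by means of Student’s" t test or Wilcoxon's rank sum test for continuous variables. The criterion is two-sided: a P "value of less than 0.05 will be considered to indicate statistical significance".
- **Randomization** sets equal allocation to three arms: "Patients will be randomized in a 1:1:1 fashion to receive EA1, EA2, and the control group". Pooled EA against control is therefore 2:1.
- **Planned number of subjects and period** gives the planning values: "the standard deviations are 19 for the test group and 25 for the control group". It adds "The expected minimum clinical difference of 20 has been defined" and "This is achieved by enrolling 25 evaluable patients in each treatment group", and then raises the number to 33 randomised per group for 20% dropout.

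No unequal-variance version of the t test is named for the two-group comparison.

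**The concern.** Student's t test estimates one common variance, weighted by degrees of freedom. With equal group sizes, unequal variances hardly matter. With unequal sizes they do: if the larger group is the less variable one, the common variance is pulled towards the smaller value, the standard error is too small and the test rejects too often.

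The plan's own figures describe that pattern. It sizes the trial with two different SDs and then names a test that assumes they are the same. The pooled comparison bears directly on the stated purpose of the trial, EA plus conventional treatment against conventional treatment alone. At stake are the false-positive rate and the interval coverage for that comparison.

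**Working it through.** **Inputs.** SD 19 (EA) and 25 (control), difference 20, two-sided 5%, 90% power, 25 evaluable and 33 randomised per arm, all from the protocol. The pooled sizes are therefore 50 versus 25 evaluable and 66 versus 33 randomised.

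**The plan's own figure.** For one EA arm against control, n = (19² + 25²)(1.960 + 1.282)² / 20² = 25.9, so 26 per arm. The stated 25 is within one patient of this, and its normal-approximation power is 0.890. Since 26/0.8 = 32.5, 33 randomised per arm follows. The calculation evidently used the two SDs as unequal values.

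**Standard errors of the pooled comparison.**

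| | 50 vs 25 | 66 vs 33 |
|---|---|---|
| Common variance | (49×361 + 24×625)/73 = 447.8 | (65×361 + 32×625)/97 = 448.1 |
| Student's SE | √(447.8×(1/50 + 1/25)) = 5.18 | √(448.1×(1/66 + 1/33)) = 4.51 |
| True SE | √(361/50 + 625/25) = 5.68 | √(361/66 + 625/33) = 4.94 |
| Ratio | 0.913 | 0.913 |

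In large samples, with n per arm, the common variance is (2×361 + 625)/3 = 449. Student's squared SE is 449×1.5/n = 673.5/n, and the true one is (361/2 + 625)/n = 805.5/n. The ratio of SEs is √(673.5/805.5) = 0.914. It does not depend on n, so a larger trial does not cure the problem.

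**Size.** The large-sample value is 2·P(Z > 1.96×0.914) ≈ 7.3%. Numerical integration over the two sample-variance distributions gives 7.32% at both 50 versus 25 and 66 versus 33. Simulation with 4 million trials per size gives 7.34% and 7.33%. Each tail holds about 3.7% instead of 2.5%. Coverage of the 95% interval is 100 − 7.3 = 92.7%.

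**Dependence on the SD ratio** (control/EA, at 66 versus 33):

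| SD ratio | Size of Student's test |
|---|---|
| 1.0 | 5.0% |
| 1.1 | 5.8% |
| 1.2 | 6.5% |
| 25/19 = 1.32 | 7.3% |
| 1.5 | 8.5% |

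**Other tests under the same SDs, equal means and normal data.**

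- Rank sum test on the pooled groups: 6.1% (50 versus 25) and 6.3% (66 versus 33), from 50,000 simulated trials each.
- Welch's t test on the pooled groups: 5.01% at both sizes.
- Student's t test on a single 1:1 pair of arms: 5.0%.
- Three-group ANOVA: about 5.1%.

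**Power for 20 points, Welch's test:** about 93% at 50 versus 25 and 98% at 66 versus 33.

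**The case against.** The strongest reply is that 7.3% is conditional. If EA had no effect of any kind, randomisation would make the distributions the same in all arms, the spreads would be equal and Student's test would hold 5%. The SDs are also weak evidence about the arm-to-arm ratio. They were taken as the largest values from a previous study, they were set alongside a 20-point difference, and the protocol does not say whether they are SDs of change or of a single reading. This stands, and it is why the size has to be given as a range over the SD ratio. It does not remove the point. The planned null concerns the changes and does not require equal spreads. The coverage shortfall also applies when EA works and the SDs differ as planned.

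Three stronger readings are tempting, and the documents do not support them:

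- **That the error favours EA.** The test is two-sided, and with equal mean changes the excess falls equally in both tails. False findings that EA is worse rise by the same amount.
- **That the pairwise EA-versus-control contrasts need the same change.** They are 1:1, and a two-arm Student's test holds about 5% there. Some inflation could arise if the Bonferroni post hoc tests used the common three-arm variance, but the protocol does not say that they do.
- **That the rank sum option is no help at all.** It removes roughly half of the excess, though not all of it.

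Two limits on scope also stand. The pooled t test is one of several planned analyses, beside the three-group ANOVA and an ANCOVA, and is not named as the sole primary test. At a true 20-point difference the statistic is about 20/4.94 = 4 standard errors at 66 versus 33, so the choice of test matters mainly for borderline results. The choice of variance form could be left to an analysis plan, but here the protocol names the equal-variance test, in conflict with its own planning SDs.

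**Conclusion.** The point holds as a conditional one. With 2:1 pooling and the planning SDs of 19 and 25, Student's test understates the standard error by about 9%. If those SDs persist with equal mean changes and roughly normal data, its size is about 7.3% at a nominal two-sided 5%, nearly half as many false positives again as stated (7.3/5 = 1.46), and 95% intervals cover about 92.7%. A reader might infer that the test simply is a 7.3% test. The documents do not support that: the size is 5.0% if the spreads are equal and 5.8% to 6.5% at SD ratios of 1.1 to 1.2. The named alternative leaves it at about 6.1-6.3%. The point is confined to the pooled two-group comparison. It is a modest flaw, worth correcting because the correction costs almost nothing.

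**What to change.** In the Statistical analysis section, name Welch's unequal-variance t test in place of Student's for the pooled EA-versus-control comparison, and base its confidence interval on the same standard error. If the two-group comparison is made by ANCOVA, specify heteroscedasticity-robust standard errors. Separate 1:1 two-arm t tests can stay as they are.

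The cost is a change of a word or two, with no extra patients. If control is the more variable group, P values become slightly larger and intervals slightly wider: at 66 versus 33 the approximate 95% half-width goes from 1.96×4.51 = 8.8 to 1.96×4.94 = 9.7 points. Power for 20 points stays above the 90% target at both the evaluable and the randomised sizes.
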